## Abstract

**Abstract:**

**Introduction:**

Care provided in people’s own homes (domiciliary care) is an increasingly important part of long-term care. There are various services, including home visits, live-in care and housing with care. Some people directly employ care staff, called personal assistants. Services vary in quality, price and availability, and there is currently little evidence of the value these services provide to the public purse and individuals. This study protocol presents planned research to fill this important gap.

**Methods and analysis:**

This will be a cross-sectional study based on surveys of care recipients, their unpaid carers as well as formal care providers. In the first half of 2026, we will survey 1850 people accessing domiciliary care either through a homecare agency, a housing with care scheme or by directly employing personal assistants and 400 unpaid carers, all based in England. We will conduct a cost-effectiveness analysis taking a ‘production function’ approach and use quality of life as measured by the Adult Social Care Outcomes Toolkit as the main outcome of interest.

**Ethics and dissemination:**

The study received ethical approval from the School of Social Sciences Staff Review Committee at the University of Kent on 20 May 2025 (reference 1195) and the Health Research Authority, London—Camberwell St Giles Research Ethics Committee on 28 October 2025 (reference 25/LO/0652). Implications around consent, data protection and confidentiality, risk and participant payment are discussed. In addition to academic outputs (eg, academic articles, conference presentations), we aim to coproduce news items and blogs with people with lived experience of accessing long-term care and jointly present findings at events aimed at the care sector. Moreover, we will offer participating care providers benchmarking briefs based on our findings.

STRENGTHS AND LIMITATIONS OF THIS STUDYCodesigning survey materials with experts by experience and offering different survey response options to participants (ie, online, post, telephone, face-to-face) to facilitate more inclusive research.Measuring care outcomes using a validated quality of life measure recommended by the National Institute for Health and Care Excellence, allowing the expression of the effectiveness of different long-term care services in terms of quality-adjusted life years.Recruiting people accessing homecare and housing with care from four geographic regions (covering about 30 local authorities) and direct employers of personal assistants from all of England to ensure national representation.Facing the risk of not achieving a sufficiently large sample, despite a comprehensive strategy to avoid a low survey response rate, which could affect the identification of statistically significant differences in cost-effectiveness.The instrumental variable approach to infer causal effects of care services on outcomes in observational studies, although having worked well in previous research, is known to be sensitive to the instrument specification.

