### Recruitment of study participants

We will recruit people who access domiciliary care by using two different approaches, based on (1) whether people access care through a homecare agency or housing with a care setting or (2) whether people directly employ a PA.

For people accessing care via a homecare agency or housing with care setting, we intend to recruit 1050 participants through their registered care location. Care locations are recruited with the help of study stakeholders, including the Homecare Association, Housing LIN, NIHR Regional Research Delivery Networks, Skills for Care and the Care Quality Commission. We aim to recruit approximately 100 homecare agencies and 50 housing with care sites across England, ideally clustered in about 30 local authorities across four regions: Yorkshire and the Humber, East Midlands, West Midlands and the South East. The care provider recruitment was initiated in May 2025. We will collect key provider characteristics through a short online survey completed by managers of care locations registering to participate in the study in November 2025 to January 2026. We will distribute survey packs to their clients in February 2026. Based on previous work, we expect around 800 responses from people accessing care via a homecare agency and 250 responses from housing with care residents.

With respect to care recipients directly employing PAs, we intend to recruit 800 participants. Recruitment will take place through Mark Bates, a specialist insurance company that holds contact details of a large number of PA employers. This approach is successfully used by Skills for Care, one of our study partners, for their annual survey of PAs and PA employers. Survey packs will be sent to approximately 17 500 PA employer email addresses.

Participants who access domiciliary care will be asked to involve their unpaid carers, should they have such support. Not all participants will have unpaid care support, and some unpaid carers may not wish to participate. Based on previous studies that adopted the route of recruiting carers via adults with care and support needs, we (conservatively) anticipate collecting responses from approximately 400 unpaid carers.^39^

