An alternative to the production function approach for identifying the impact of LTC services on care recipients’ QoL applies a counterfactual self-estimation method. ASCOT-INT4 asks participants to report both their QoL at the time of survey but also their ‘expected’ QoL in the hypothetical situation in which they would not have access to LTC services. This allows the calculation of self-reported QoL gain (ie, impact of services). Although subject to its own limitations, the methodology has been shown to be feasible and to provide similar estimates to the IV method.^30^ Therefore, where possible, we will compare these results to those of the IV analysis. Ideally, where cost-effectiveness estimates using both approaches coincide, this could provide evidence of the robustness of our findings. Where estimates differ, the direction and size of the discrepancy can also be assessed to further understand the limitations of the two approaches.

For comparative cost-effectiveness analysis between care settings, the most common approach to address the issue of self-selection bias is using matching techniques like, for example, Propensity Score Matching.^24 41 42^ By matching individuals with similar observed characteristics from the two groups (eg, gender, age, ethnicity, underlying health issues and difficulty with ADLs), the differential effect of the care services on care recipients’ QoL can be identified if assignment to groups is random conditional on controls.^43^

The same matching technique can be used for the comparative analysis between modes of domiciliary care.

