Our ambition is for our research to have an impact on several domains of the LTC system in England and the people accessing it. Project findings could inform policy decision-making to support people with care needs to live more independent lives, provide guidance about domiciliary care options, as well as support individuals and families to make more informed decisions about care. More specifically, estimates of the relative cost-effectiveness of domiciliary care could help policy makers setting public budgets (eg, inform Spending Reviews) and developing guidance to encourage home and community-based care options (eg, White Papers). Research findings could also inform practice, especially care commissioning choices by both public commissioners and individual purchasers (eg, through NICE guidance). Finally, a more direct impact on the QoL outcomes of people who access domiciliary care could be achieved through the benchmarking briefs provided to participating care providers, which may help managers identify aspects of their services where improvement would make most difference.

We also have to acknowledge a number of risks and limitations of this study. For example, the analysis relies on the successful recruitment of sufficiently large samples of homecare agency clients, housing with care residents and PA employers. Not achieving minimum sample requirements may limit the identification of statistically significant differences in cost-effectiveness, where this may exist in reality. The study team took a rather conservative approach when considering expected response rates and planned a comprehensive strategy to reduce the risk of a potential low response, including: (1) sub-contracting the data collection activity to social research specialists, (2) sending client communications and reminders through recruited providers, (3) offering alternative options of completing the survey (ie, paper, online, telephone or face-to-face), (4) setting up a helpline to respond to participants’ queries and arrange interviews (including in languages other than English), (5) visits to housing with care sites by the fieldwork team to encourage and support survey completion and (6) offering respondents high-street vouchers as a ‘thank you’ for taking part. We trust that these mitigating actions will help achieve sufficiently large and balanced subsamples.

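### The agency-versus-PA comparison sets a mainly four-region sample against an all-England one, and no area variable is named for the matching, so part of any difference may reflect area

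*Protocol article*

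**What the plan says.** **Sampling frames.** The strengths and limitations box in the abstract says the study will recruit people using homecare and "housing with care from four geographic regions (covering about 30 local authorities) and direct employers of personal assistants from all of England", and presents this as securing national representation. Recruitment of study participants describes care locations as "across England, ideally clustered in about 30 local authorities across four regions". The clustering is therefore an aim, not a fixed rule.

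**Contact routes.** For agency and housing clients, who are recruited through their care location, the same section says "We will distribute survey packs to their clients in February 2026". For the PA group, "Survey packs will be sent to approximately 17 500 PA employer email addresses", using an insurance company's contact list. The Discussion adds an activity specific to housing: "visits to housing with care sites by the fieldwork team to encourage and support survey completion". The completion options (paper, online, telephone, face-to-face) are the same for everyone.

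**Analysis.** Data analysis proposes propensity score matching for comparisons between care settings, with example variables "eg, gender, age, ethnicity, underlying health issues and difficulty with ADLs". It continues: "The same matching technique can be used for the comparative analysis between modes of domiciliary care". The stated condition is that group membership is random given the controls. The Cost-effectiveness section defines the estimand as the average treatment effect on the treated.

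**Local policy.** Data analysis also justifies the instrument by differences between local authorities in policy and resources, so that people with equal needs in different places can get different amounts of support.

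**Planning values.** Sample size calculations expects an agency-PA difference of 0.02 to 0.03 with SD 0.188, and plans 800 per group.

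**The concern.** Outside the sampled authorities, PA employers can enter the study but agency clients largely cannot. Area therefore predicts group membership by design. The article itself says area changes the care that similar people receive, and care received is the route by which the study expects QoL to change. A variable that is linked to both group and outcome is a confounder of the agency-PA comparison. Matching on age, gender, ethnicity, health and ADLs does not remove it.

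The estimand makes this concrete. If PA employment is the treated condition, the counterfactual for a PA employer outside the four regions is built from agency clients who live elsewhere. If agency care is the treated condition, agency clients can be matched to PA employers anywhere in England.

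The expected difference is small, so a modest area offset could create, hide or reverse it, and it would then be read as an effect of the type of care. The limitations discussed in the article cover sample size, the instrument and functional form. They do not mention the difference in frames.

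**Working it through.** **1. Reproduce the planned sample size.** Inputs from Sample size calculations: SD 0.188, alpha 0.05 (taken as two-sided), power 80%. With n per group = 2 × (1.96 + 0.8416)² × SD² / d²:

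- d = 0.03 gives 617 (article: 616).
- d = 0.02 gives 1388 (article: 1389).

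The article's figures reproduce. A one-sided test would give 486 and 1093, which do not fit.

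**2. Precision at the planned size.** SE = 0.188 × √(2/800) = 0.0094. The difference detectable with 80% power is 2.8016 × 0.0094 = 0.026. Power is 57% at 0.02 and 89% at 0.03. Clustering and losses from matching are ignored here.

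**3. Effect of an uncorrected offset b when there is no true difference.** Rejection rate = Φ(b/SE − 1.96) + Φ(−b/SE − 1.96).

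| Assumed offset b | b/SE | Rejection rate |
|---|---|---|
| 0 | 0 | 5% |
| 0.004 | 0.43 | 7% |
| 0.01 | 1.06 | 19% |
| 0.02 | 2.13 | 57% |

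**4. What offset is possible?** The document gives no area gap in QoL and no regional split of PA employers, so both are assumed. Take area bias = (share of PA employers outside the sampled regions) × (mean QoL gap between areas):

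- Low end: 40% × 0.01 = 0.004.
- Middle: 50% × 0.02 = 0.010.
- High end: 70% × 0.03 = 0.021.

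The range runs from small to about the lower end of the expected effect. It shows sensitivity and is not an estimate.

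**5. What a common-area analysis could deliver.** Assume PA responses are spread evenly and four of nine English regions are sampled. Then 800 × 4/9 ≈ 356 PA employers remain. Detectable difference = 2.8016 × 0.188 × √(1/800 + 1/356) = 0.034, which is above the whole expected range. If the share in the sampled regions is instead 30% to 60% (240 to 480 people), the detectable difference runs from 0.039 to 0.030. Power is then 30% to 45% at 0.02 and 58% to 79% at 0.03.

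**The case against.** **The matching list is illustrative.** It is introduced as examples, matching is something that can be used for modes of care, and a journal article leaves the final covariates to fuller documents. A reader might infer that area will be left out and that local policy will be credited to type of care. The document does not support that. It supports only that area may be mixed into the comparison unless it is controlled, and that the article does not say it will be.

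**Wider confounders are collected.** Data requirements lists financial situation, housing conditions and access to the local area and facilities. The local-area instrument also needs respondents' area wherever it is used. This stands, and it makes the remedy cheap. However, the authority commissioning data listed there come through the registered care location, a source described only for the provider-based groups.

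**The instrument argument concerns amount of care.** It assumes that local policy acts on QoL only through formal care. That is correct, but it does not remove the problem: a difference in QoL that arises because areas provide different amounts of care would still appear in the matched comparison as an effect of type of care.

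**Completion mode is not a stated group difference.** A reader might infer from the email route and the housing visits that survey mode will distort the comparisons. All participants have the same options, and the document gives no mode effect on QoL. An imbalance is plausible, so recording it is reasonable, but bias is not shown.

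**Housing with care.** Agency and housing clients share the same regions. The area argument does not extend to that comparison.

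**Conclusion.** The concern holds as a risk that the article leaves open. The frames for agency clients and PA employers differ geographically. The article's own account of local policy makes area a plausible confounder, and none of the named matching examples is an area measure. Against an expected difference of 0.02 to 0.03, an offset of 0.01 would be enough to raise the false-positive rate from 5% to about 19%.

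The offsets are assumed, and the document allows neither their size nor their direction to be derived. The rates also assume 800 independent responses per group and SD 0.188. No figure stated in the article is wrong on this point. The conclusion is limited to comparisons that involve PA employers.

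Separately, the claim of national representation is too strong for the agency and housing groups, whose recruitment is concentrated in four regions.

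**What to change.** 1. For comparisons with PA employers, include authority-level covariates in the matching or outcome model, for example deprivation, rurality, and authority spend or fees. Take them from a source that covers both groups, not from the care-location survey.
2. Add a sensitivity analysis restricted to PA employers in the sampled regions, labelled in advance as supportive because of its limited precision.
3. Record completion mode and help received, report both by group, and adjust for them in a sensitivity analysis.
4. In the strengths and limitations box, replace the claim of national representation with the actual coverage of each group.

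The cost is mainly analysis-plan wording, plus linking respondents' authority to area data and keeping the response mode from fieldwork.

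Two more drastic steps are not advised. Exact matching on region as the main analysis would discard PA employers outside the sampled regions and reduce that analysis to the precision of item 2. Restricting to people who completed unaided could select on disability differently in each group and so add bias.

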## Introduction

 In most Organisation for Economic Co-operation and Development countries, the focus of long-term care (LTC) provision is shifting away from institutional settings (eg, residential and nursing care) to support people to live independent lives for longer in their own homes.^1^,^3^

Similarly, in England, the ambition expressed in the Department of Health and Social Care’s policy paper on *Adult social care priorities for local authorities: 2026 to 2027* is for people to be able to access care and support earlier and closer to home.^4^ Nonetheless, there are several challenges in achieving this change. For instance, there are issues relating to care staff wages, recruitment and retention, often linked to low fee rates, which could also affect care provider quality,^5^ with providers most affected handing back contracts to public commissioners or even going out of business.^6^ Moreover, people have different support needs, values and preferences, and not all options are suitable for (or acceptable to) everyone.^1 3 7^

The size of the domiciliary care market in England is not accurately recorded. Available statistics are for the community-based (ie, non-residential) market, which includes services like day care along with services in people’s own homes, like visiting and live-in care provided by domiciliary (or home) care agencies, housing with care (eg, extra care housing or retirement villages) and services by carers directly employed by care recipients (called ‘personal care assistants’ or ‘personal assistants’; PAs). Estimates put community-based care recipients in March 2023 in the region of 585 000, with about 450 000 supported (fully or partially publicly funded) by local authorities^8^ and about 135 000 (23%) self-funding their care.^9^ Community-based care in England is provided by about 15 000 largely independent care locations and about 100 000 PAs.^10^

This study protocol has been developed following a scoping study (NIHR203902), in response to a call by the National Institute for Health and Care Research (NIHR) for research on ‘*Understanding the economic case of domiciliary care*’ (NIHR PRP 31–02-04). The scoping study included the assessment of existing evidence and available research resources (eg, data), as well as consultation with sector stakeholders, policy makers and people with lived experience of LTC about the questions and approaches for an economic evaluation study.

An international scoping literature review on cost-effectiveness analysis of domiciliary care, undertaken by members of the study team, showed that the research evidence on the economics of domiciliary care is limited and methodologically inconsistent.^11^ While many studies included both benefits and costs in their assessment of cost-effectiveness,^12^,^19^ a number of them looked only at outcomes^20^,^23^ or only at costs.^24 25^ There were also differences in outcome measures and the costs of care considered, and only a few studies used methods that considered selection problems due to unobserved confounders.^13 14 24^ All this highlighted the importance of using statistical methods that take into account selection issues when identifying the true impact of care services on care outcomes.

The assessment of existing resources did not lead to the identification of any suitable data for the evaluation of the cost-effectiveness of care services in England. National datasets (eg, the Adult Social Care Survey and the Adult Social Care Client Level Data) do not allow linking information of care inputs to care outcomes, and provider Digital Social Care Records do not include validated care outcome measures and, due to data protection issues, are not yet made available for research. Therefore, we had to include primary data collection in the research plan.

Finally, sector stakeholders confirmed during the consultation that an assessment of the benefits and costs of care services in England is highly relevant, as: (1) it could provide care commissioners with evidence on value for money of different care services and the most net beneficial option for different groups of people with care needs (eg, by age group and level of care needs); (2) it could assist policy makers in identifying the comparative value of supporting more people (ie, extending eligibility for public LTC support) as opposed to increasing the intensity of care for people already supported and (3) it could offer people with care needs self-funding their care (and their families) greater insights into the value of different care options, so more informed decisions can be made.

### Aims and objectives

The main aim of the study is to evaluate the value for money of domiciliary care. In this respect, we will assess the comparative cost-effectiveness between:

People with different levels of care needs;Modes of delivery (eg, homecare agencies vs directly employed PAs);Different care settings (ie, residential care and housing with care).

To capture the broader societal impact of domiciliary care, we will assess its effects on healthcare demand (eg, potentially avoidable hospitalisations) as well as on unpaid carers’ quality of life (QoL) and other outcomes (eg, health and formal employment).

To deliver our aim and objectives, we have organised the study in four work packages, as shown in the flow diagram in figure 1.

**Figure 1 F1:**
[figure not shown]
Flow diagram. CQC, Care Quality Commission; DACHA, Developing research resources And minimum data set for Care Homes’ Adoption and use; DHSC, Department of Health and Social Care; HCA, Homecare Association; HLIN, Housing Learning and Improvement Network; HRA, Health Research Authority; NHS, National Health Service; NIHR, National Institute for Health and Care Research; PAs, personal assistants; PPIE, patient and public involvement and engagement; RG, research governance; RRDN, Regional Research Delivery Network; SfC, Skills for Care; WP, work package.

